## Abstract

**Background:**

Advancing evidence-based, tailored interventions for substance use disorders (SUDs) requires understanding temporal directionality while upholding ecological validity. Previous studies identified loneliness and craving as pivotal factors associated with alcohol consumption, yet the precise directionality of these relationships remains ambiguous.

**Objective:**

This study aims to establish a smartphone-based real-life intervention platform that integrates momentary assessment and intervention into everyday life. The platform will explore the temporal directionality of contextual influences on alcohol use among individuals experiencing loneliness and craving.

**Methods:**

We will target 180 individuals aged 18 to 70 in Germany who report loneliness, alcohol cravings, and meet risk or binge drinking criteria (over 14 standard drinks per week or five drinks in a single day for males, and over seven drinks per week or four drinks in a single day for females). Using a Within-Person-Encouragement-Design and Just-In-Time-Adaptive-Interventions, we will manipulate the contexts of loneliness and alcohol craving with cognitive reappraisal and physical activity interventions against a control condition (working memory task).

**Results:**

Recruitment started in June 2024, with data collection and processing expected by June 2027.

**Conclusion:**

Our real-life intervention platform endeavors to serve as a robust tool for discerning the directionality of the effects from time series data in everyday life influences on alcohol use for the future study. Ultimately, it will pave the way for low-threshold prevention, clinical treatment, and therapy to target diverse contexts of everyday life in SUD.

**Trial registration:**

German Clinical Trials Register DRKS00033133.

## Introduction

The desire for social connection is one reason people consume substances such as alcohol and cannabis.^1,2^ Increased substance use can heighten the risk for substance abuse and dependence. In Germany, up to 19% of the population engage in hazardous drinking.^
3
^ Previous studies have identified loneliness and craving as significant factors associated with alcohol consumption. However, the precise temporal direction of these relationships—critical for establishing causality—remains unclear.^4,5^ To ascertain the temporal direction of these contextual correlates for real-life treatment targets, adopting an ecological approach to momentary intervention is required. Therefore, the objective of this study is to establish a real-life intervention platform aimed at testing temporal directionality through experimental manipulation in everyday life, particularly in the context of loneliness and alcohol craving.

Loneliness, as the distressing experience of a discrepancy between one's desired and actual social connection,^
6
^ correlates with adverse health behaviors such as increased alcohol use and physical inactivity.^
2
^ A Eurofound survey conducted in 2016, prior to the pandemic, revealed that 12% of EU citizens experienced loneliness more than half of the time. This figure doubled to 25% during the first COVID-19 outbreak, with an additional 15.5% of individuals reporting feeling lonely more than half of the time.^
7
^ Loneliness had a strong effect on alcohol consumption among alcohol use disorder (AUD) participants across age groups.^
4
^ In particular, the sequential latent class regression models in our previous study showed that loneliness predicted change in alcohol consumption patterns over time in subsamples including adolescents and young adults, and middle-aged men.^
8
^

Craving, as “an intense desire or urge” for substances, is described as a consequence of the conflict between the need to consume substance and the desire to abstain; it is recognized as one cardinal symptom of AUD and serves as a major relapse predictor.^
9
^ Craving is not only an established marker for diagnoses on a cross-sectional and retrospective assessment level, but also evidenced to correlate with substance use on a within-subject and momentary level in everyday life: the more a person craves a substance at a given moment, the higher the consumption is, and vice versa.^
1
^ Recent studies argue for craving to be a promising causal marker with prognostic value and high potential as a treatment target for interventions triggered by ecological momentary assessment (EMA).^
10
^

The EMA methodology (e.g. smartphone-based electronic diaries and wearables) enables to investigate intra- and interindividual effects as well as reciprocal relationships.^11,12^ EMA involves repeatedly sampling of individuals’ behaviors and experiences in real-time within their natural environments. This method minimizes recall bias and enhances ecological validity, while approximating temporal dynamics (e.g. Granger causality).^
13
^ However, EMA can also impose a burden on participants, requiring them to respond to repeated questionnaires throughout the day, which may disrupt ongoing activities and cause distress.^
14
^ We can apply EMA to gather intensive longitudinal data (ILD) on determinants and consequences of drug intake.^
15
^ On the one hand, ILD is more ecologically valid, as it directly measures the subjects’ experience in their current environment; on the other hand, it allows to approximate temporal associations. However, causal inferences can only be established if: (1) variables of interest are correlated with each other, (2) a temporal order is given, (3) hidden third variables are controlled or explained; and (4) the direction of the effect is indispensable (e.g. heightened levels of craving usually correspond to increased alcohol consumption).^
16
^ Accordingly, experimental designs enable to test for causality through experimental manipulation under laboratory conditions and control of potential hidden influences.^
17
^

To approximate causality and test temporal directionality underlying drug intake in everyday life, we need to combine the advantages of laboratory and ambulatory approaches. This combination allows us to achieve both ecological validity and approximate causal temporal inferences (i.e. an ecological approach to intervention). EMA enables the collection of time series data, which can be used to approximate the temporal necessity of causality, known as Granger causality (i.e. where the cause precedes the effect).^
18
^

Just-In-Time-Adaptive-Interventions (JITAIs)^
19
^ are recognized as a first key step toward approximating causality within subjects in everyday life.^
20
^ In essence, JITAIs use real-time analyses to determine momentary states (e.g. EMA of loneliness and alcohol craving and device-based read-outs, such as acceleration signals for physical activity detection), and controlled or randomized intervention-assignments (e.g. an instruction to engage in physical activity after a couple of high-craving ratings). However, experimental manipulations may be infeasible in everyday life due to practical or ethical reasons (e.g. participants may be unable to interrupt their task to follow intervention-instructions under high work-related stress).

Here, the Within-Person-Encouragement-Design (WPED)^
21
^ offers a viable solution through three key elements: (1) smartphone-based, randomly assigned encouragement to engage in an intervention as an instrumental variable (Encouragement), (2) the intervention (i.e. cognitive reappraisal, physical activity) itself (Treatment), (3) target variables (i.e. loneliness and alcohol craving) that are to be causally influenced by the Treatment (Outcome). Based on an instrumental variable estimation approach, a causal treatment effect on the outcome can be analyzed if a correlation between the encouragement and the treatment is present and given the theoretical assumption that any encouragement effects on the outcome are fully mediated by the treatment. The WPED combines three major approaches: (1) multilevel analyses of within-subject mechanisms, (2) experimental within-subject manipulation of the “treatment” variable, and (3) randomized encouragement as an instrumental variable to induce exogenous experimental variation if consistent adherence to the “treatment” is not realistic.

Both cognitive reappraisal and physical activity have been associated with reduced loneliness and alcohol craving.^22–26^ At the behavioral and neurobiological levels, both can improve cognition functions.^27,28^ However, they are very different in nature: on the one hand, cognitive reappraisal is a collection of “structured, goal-directed, and collaborative intervention strategies that focus on the exploration, evaluation, and substitution of the maladaptive thoughts, appraisals, and beliefs that maintain psychological disturbance.”^
29
^ In the context of AUD, at low engagement in reappraisal, greater startle reactivity to uncertain threat was associated with greater problem alcohol use.^
30
^

On the other hand, physical activity describes a broad wealth of human movements ranging from distinct types of exercise (e.g. dancing, jogging as a structured physical activity characterized by high energy expenditure and prolonged duration for a fitness goal) to different nonexercise activities (NEAs; i.e. all other daily physical activities including walking and stair-climbing, or sedentary breaks such as short-term movement programs), with the latter NEA especially qualifying for JITAI served by smartphone applications.^31,32^ The type, duration, and intensity of physical activity can be tailored toward individual preferences and improvements of specific symptoms. Physical activity is a promising adjunctive treatment for substance use disorder (SUD)^
33
^ and benefits SUD patient care^
34
^; e.g. it has been associated with reductions in craving across different substances (e.g. tobacco, marijuana, alcohol), and especially in AUD, several studies indicate that physical activity can decrease craving for alcohol.^
35
^ In particular, the recent literature assumes that “craving could be specifically targeted by short and easily achievable physical exercise” and short bouts of moderate physical activity such as brisk walking are correlated with reduced craving.^
36
^

Therefore, given both these proven benefits of cognitive reappraisal and physical activity for SUD prevention and treatment as outlined above, shown in Figure 1, and their high suitability for momentary application in everyday life (e.g. short yet effective cognitive reappraisal and physical activity programs guided via smartphone application), they qualify as highly promising tools and interventions in intensive longitudinal research for experimental manipulation in everyday life to elucidate the real-life causality of change among individuals with SUDs.^37,38^ Depending on the momentary settings (e.g. in work or leisure time) and personal preferences as well as momentary cognitive capacities, either the cognitive reappraisal or the physical activity intervention may be better suited to, for example, reduce momentary loneliness and alcohol craving.

**Figure 1. fig1-20552076241311731:**
[figure not shown]
Schematic overview of daily life causality testing in our study. Systematic experimental manipulation in phases of momentary loneliness/alcohol craving levels through the incorporation of cognitive reappraisal (Intervention 1), physical activity (Intervention 2), and working memory (control condition) via interactive smartphone triggers will allow to test for the (non)causal nature of real-life correlates (e.g. loneliness and alcohol craving) of alcohol intake.

Therefore, the overarching aim of our study is to establish a real-life intervention platform that incorporates a JITAI^
39
^ into everyday life to test the temporal direction of factors that lead to substance use. Our approach positions us uniquely to: (1) understand the temporal directionality of mechanisms of substance use in everyday life, (2) set the evidence-basis for an increasing number of (digital) mental health interventions designed for substance use through separating disease causes from consequences, (3) guide JITAIs^
19
^ for the right type/amount/time of support by adapting to individuals’ changing internal and contextual states.

We hypothesize (H1) that cognitive reappraisal and physical activity interventions will reduce momentary loneliness (H1a) and/or alcohol craving (H1b). In addition, we assume (H2) that decreases in momentary loneliness and/or alcohol craving will correspond to a decrease in real-life alcohol consumption.

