**Figure 4. fig4-20552076241311731:**
[figure not shown]
Illustrative screenshots from the comic elucidating cognitive reappraisal. This comic was created by us using the AI image generator Midjourney.

The JITAI will take approximately 6 min. It will begin by prompting participants to describe the situations in which they encountered feelings of loneliness or cravings. Subsequently, they will be asked to articulate the thought that most triggers their loneliness or craving. Finally, participants will be tasked with documenting how they challenge this thought, employing four reappraisal strategies.^
60
^ (1) Considering disadvantages: What are the disadvantages of thinking like this if I want to reach my goals to drink less or not to feel lonely. (2) Checking reality: Have I had any experiences to show that this mental statement is not always true? (3) Use other people as a reference point: What would someone who knows to handle this situation well say if they knew I was trying to reduce my drinking/not to feel lonely? (4) Imagine giving advice: What advice could you give to a close person in a similar situation? After each reappraisal, participants will be asked to rate their conviction regarding the thought related to loneliness or craving on a horizontal Visual Analog Scale (VAS)^61,62^ ranging from 0 (“not convinced at all”) to 10 (“strongly convinced”). In addition, they will be prompted to assess the difficulty of reappraising the specific situation using a horizontal VAS ranging from 0 (“strongly disagree”) to 10 (“strongly agree”).

*Intervention 2 (physical activity)*. The physical activity intervention will be designed to increase participants’ step count within a set timeframe. Previous studies have been found that moderate-intensity exercise sessions lasting 5 to 15 min can significantly reduce alcohol cravings.^36,63–65^ Accordingly, our physical activity intervention encourages participants to take a brisk 6-min walk (or engage in indoor walking). During this activity, the number of steps per minute is tracked using a *movisens* Move4 wrist-sensor, providing participants with real-time feedback on their walking pace. Control measures involve automatically assessing the number of steps taken during exercise using the *movisens* Move4 activity sensor.

*Active control (a gamified working memory task)*. The working memory is facilitated by the Great Brain Experiment app,^
66
^ which has been tested and validated in German.^
50

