## Expected results

We anticipate that our platform will demonstrate feasibility in administering both cognitive reappraisal and physical activity interventions, which are expected to reduce cravings and loneliness. In addition, it will facilitate the integration of experimental manipulation into participants’ daily routines, enabling effective testing of causal relationships. We expect that both cognitive reappraisal and physical activity interventions will decrease momentary loneliness (H1a) or/and alcohol craving (H1b). Furthermore, we posit that decreases in momentary loneliness and alcohol craving will be associated with a reduction in real-life alcohol consumption (H2).

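### Figure 1 promises a test of whether loneliness and craving cause drinking, but the randomised encouragement, as analysed, identifies only the interventions' effects on those two states

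*Protocol article*

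**What the plan says.** **The claim.** The Figure 1 caption says the manipulation "will allow to test for the (non)causal nature of real-life correlates (e.g. loneliness and alcohol craving) of alcohol intake". Participants and recruitment likewise gives the testing of causality as the reason for the target sample, and Expected results anticipates effective causal testing.

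**The interventions.** The Introduction states "Both cognitive reappraisal and physical activity have been associated with reduced loneliness and alcohol craving". Expected results says of the two interventions, "which are expected to reduce cravings and loneliness". No intervention is assigned to one state. H1 joins the states with and/or. H2, at the end of the Introduction, is that "decreases in momentary loneliness and/or alcohol craving will correspond to a decrease in real-life alcohol consumption".

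**Reappraisal content.** In Design and procedure, the first reappraisal strategy asks "What are the disadvantages of thinking like this if I want to reach my goals to drink less or not to feel lonely". The third asks what a person who copes well would "say if they knew I was trying to reduce my drinking/not to feel lonely". The evening response-inhibition task is included partly to examine cognitive function as a further mediator in relation to problematic drinking.

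**The analysis.** The Introduction states the exclusion assumption for the step from encouragement through treatment to outcome, and defines the outcome as loneliness and craving. The two-level path model in Data analysis has the same endpoints. Changes in alcohol consumption are tested by multilevel modelling outside that model.

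**The concern.** Three links have to be kept apart: encouragement to treatment, treatment to state, and state to drinking. Encouragement is randomised, so the first can be estimated directly and the second through the instrument, under the stated exclusion assumption. The third has no instrument of its own. It could borrow the randomisation only if the interventions moved loneliness and craving in clearly different proportions and affected drinking through nothing else. The article states neither condition, and its own prompts and its cognitive-function pathway put the second in doubt.

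At stake is how the drinking result is read. A fall in drinking after encouragement could be credited to loneliness when it came through craving, or through renewed attention to a drinking goal. A null result could be reported as showing a state to be non-causal when encouragement never moved that state.

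**Working it through.** **1. The plan's own figure.** Sample size and power considerations gives 6350 data points: 180 × 0.8 = 144, and 144 × 21 × 3 × 0.7 = 6350.4. It reproduces, but it has no bearing on this point, which concerns identification rather than precision.

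**2. What separating the states would require.** Let reappraisal (R) and physical activity (P) change loneliness by l_R and l_P and craving by c_R and c_P, each against control. Let b_L and b_C be the effects of the states on drinking, and d a direct effect of reappraisal on drinking. The effects on drinking are then

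- y_R = l_R·b_L + c_R·b_C + d
- y_P = l_P·b_L + c_P·b_C

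Setting d = 0 and solving, with D = l_R·c_P − c_R·l_P:

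- b_L = (y_R·c_P − c_R·y_P)/D
- b_C = (l_R·y_P − l_P·y_R)/D

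The article gives no effect sizes, so all values below are assumptions in SD units. The planned analysis does not contain these equations; they show what the causal claim would need.

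**3. Equal profiles.** All four state effects are −0.20. D = 0.04 − 0.04 = 0, so there is no solution and the states cannot be separated.

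**4. Clearly different profiles, no direct path.** l_R = −0.30, c_R = −0.05, l_P = −0.05, c_P = −0.30; truth b_L = 0, b_C = 0.30. D = 0.09 − 0.0025 = 0.0875. y_R = −0.015 and y_P = −0.09.

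- b_L = (0.0045 − 0.0045)/0.0875 = 0
- b_C = (0.027 − 0.00075)/0.0875 = 0.30

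The truth is recovered, so separation is possible in principle.

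**5. As step 4, with d = −0.06.** y_R = −0.075 and y_P = −0.09.

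- b_L = (0.0225 − 0.0045)/0.0875 = 0.206 (truth 0)
- b_C = (0.027 − 0.00375)/0.0875 = 0.266 (truth 0.30)

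With neither state causal, y_R = −0.06 and y_P = 0. Then b_L = 0.018/0.0875 = 0.206 again, and b_C = −0.003/0.0875 = −0.034.

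The error in b_L is d × (−0.30)/0.0875. It is 0.07 for d = −0.02, 0.21 for −0.06 and 0.34 for −0.10. More data do not reduce it.

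**6. Regressing drinking on the two states (an H2-type analysis).** Assume a shared cause with unit variance and loading 0.5 on loneliness, craving and drinking, and residual SD 0.85 for each state. Each state then has variance 0.25 + 0.7225 = 0.9725, and their covariance is 0.25. Each coefficient is biased by 0.5 × 0.5/(0.9725 + 0.25) = 0.20. With loadings of 0.25 the bias is 0.25 × 0.25/(0.785 + 0.0625) = 0.07; with no shared cause it is 0. Association is therefore the right label for this link.

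**The case against.** The strongest reply is that the article is mostly careful. It speaks of approximating causality and of temporal directionality, and H2 is worded as correspondence. That stands: H1 and H2 as worded are not at fault. The fault is in the stronger claim in Figure 1 and its echoes.

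Four stronger readings are tempting, and the documents do not support them.

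- *A drinking change can never be attributed to a state.* Step 4 shows that it can if profiles differ clearly and no other path exists. H1 says and/or, and the Introduction calls the interventions very different in nature and says either may suit a given situation better. Joint lowering is expected, not certain.
- *Separating loneliness from craving is the trial's main promise.* No section says so.
- *Reappraisal targets drinking itself throughout.* Both quoted prompts offer a loneliness alternative, possibly matched to the situation. A direct path is plausible, not shown, and least evident on loneliness-only occasions.
- *The recorded trigger types (loneliness alone, craving alone, both) are ignored.* Such analyses may stand in an analysis plan that is not shown, so their absence from the article is no fault.

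Nor can a loss of precision be quoted. No instrumental-variable analysis of drinking is described, and any figure would depend on assumed profiles and on how the encouragements are allocated.

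**Conclusion.** The point holds in conditional form. As described, randomised encouragement identifies treatment effects on loneliness and craving. It does not identify the effect of either state on drinking, so the (non)causal claim exceeds the stated analysis. A drinking effect or its absence is not attributable to one state unless the effect profiles clearly differ and neither intervention reaches drinking by another route. The article asserts neither condition.

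The documents supply no effect sizes, so the size of the error cannot be fixed. The 0.07 to 0.34 range for a spurious loneliness effect rests wholly on the assumed profiles and direct effects. H1, the sample size and the conduct of the study are unaffected; what changes is the interpretation of the drinking result.

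**What to change.** 1. Estimate the effect of randomised encouragement on drinks recorded after the trigger, over a window fixed in advance, and report it as an effect of the intervention, not of one state. Give it by trigger type as exploratory only. Those strata do not close a direct drinking-goal path, and a non-significant effect on the other state must not be read as zero.
2. Report the state-to-drinking link (H2) as association or temporal order.
3. If a mediated, state-specific causal reading is wanted, state the exclusion assumption from intervention through state to drinking, and add a sensitivity analysis over a range of direct effects.
4. Do not conclude that a state is (non)causal where encouragement did not demonstrably move it. If items 3 and 4 are not adopted, drop that wording.

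Cost: extra analysis text and a narrower claim. No new data are needed, since drinks are assessed eight times a day and the trigger situation comes from the momentary ratings. The trigger-type estimates will be imprecise.
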